### 2.5. Allocation and Randomization

The randomization sequence will be generated by an independent statistician not involved in participant recruitment or outcome assessment. Randomization will be conducted prior to study initiation using Research Randomizer v4.0 [58]. Block randomization with a block size of three will ensure an equal number of participants across the three study groups [59]. A total of 54 participants will be allocated in 18 blocks of three, with each block containing one assignment to each group (1 = control, 2 = TENS, 3 = PENS), without repetition or predetermined order.

Stratified randomization by graft type or concomitant procedures was not implemented; participants were randomized without stratification to maintain study feasibility and integrity.

To ensure allocation concealment, the generated randomization sequence will be implemented using individual, sequentially numbered index cards indicating the assigned group. The cards will be placed in sealed opaque envelopes, which will be opened only after baseline assessments are completed by an independent assessor. This approach prevents recruitment and enrollment personnel from predicting future allocations, even with block randomization of size three. By combining independent sequence generation with secure envelope implementation, selection bias is minimized while ensuring correct assignment of the intervention.

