### 2.3. Sample Size Calculation

Sample size was calculated using G*Power software (version 3.1) [52] for a repeated-measures analysis of variance with three groups. Assuming a medium effect size (f = 0.25), a power of 80% (β = 0.20), and a two-sided significance level of α = 0.05, a total sample size of 45 participants was required. The calculation was based on a correlation among repeated measures of 0.5 and a nonsphericity correction factor (ε) of 1. To account for an anticipated dropout rate of 20%, a total of 54 participants will be recruited, with 18 allocated to each group (control, TENS, and PENS).

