### 2.4. Participants and Eligibility Criteria

Eligible patients will be aged 18–55 years old and will have undergone ACLR within the previous six weeks using hamstring tendon (HT), patellar tendon (BPTB), quadriceps tendon autografts, or allografts at Clínica CEMTRO. ACLR may be accompanied by concomitant surgical procedures on one or both menisci (repair, debridement, rasping, partial meniscectomy) and/or a Lemaire lateral extra-articular tenodesis. All patients will provide written informed consent.

Exclusion criteria will include: (1) contraindications for invasive procedures [53]; (2) contraindications for dynamometric assessment [41]; (3) history of lumbar hernia or protrusion; (4) receipt of alternative treatments outside the study (e.g., analgesics); (5) neuropathic pain in the lower limbs; (6) central nervous system disorders [39]; (7) history of neurological disorders or spinal surgery; (8) inability to reliably complete self-reported questionnaires [54]; (9) Personal Psychological Apprehension Scale score > 37.5 [55]; (10) absence from scheduled measurement sessions; and (11) voluntary withdrawal from the study.

The Personal Psychological Apprehension Scale (PPAS) is a valid and reliable instrument that provides a useful tool for assessing participants’ subjective perceptions. The PPAS consists of 15 items, each with four response options: (1) very rarely, almost never; (2) occasionally, hardly ever; (3) frequently, quite often; and (4) continuously, almost always. Total scores range from a minimum of 15 points to a maximum of 60 points [55].

This criterion is applied to ensure participant safety and compliance, because individuals with high psychological apprehension may experience discomfort or adverse reactions during the intervention. Notably, the same PPAS-based exclusion criterion has been applied in previous studies involving invasive physiotherapy interventions [56,57].

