### 2.9. Statistical Methods

All statistical analyses will be performed using SPSS statistical software for Windows (version 27.0; SPSS Inc., Chicago, IL, USA). The primary analysis will be conducted according to an intention-to-treat approach, using linear mixed-effects models, which accommodate repeated measures and handle missing data under the missing-at-random assumption.

A complementary per-protocol analysis will be conducted as a sensitivity analysis, including only participants who complete the assigned intervention and all scheduled assessments according to predefined criteria. This dual approach allows evaluation of the robustness of the primary findings.

Data normality will be assessed using the Shapiro–Wilk test. Descriptive statistics will be calculated for baseline characteristics, reporting means and standard deviations for normally distributed variables, and medians with interquartile ranges for non-normally distributed variables.

To evaluate intervention effects over time, repeated-measures analysis of variance (ANOVA) will be applied to outcomes meeting normality assumptions. The within-subject factor will be time (pre-treatment, immediate post-treatment, 24 h post-treatment, and 7 days post-treatment), and the between-subject factor will be group (control: CRP only; TENS: CRP plus a high-frequency TENS session; PENS: CRP plus a LTP PENS session). Bonferroni correction will be used for post hoc comparisons. Sphericity assumptions will be assessed, and Greenhouse–Geisser corrections will be applied as appropriate.

To provide a more flexible and robust analysis of repeated measures, linear mixed-effects models will additionally be applied. These models will include the fixed effects of group, time, and the group × time interaction. They allow inclusion of all available data and appropriately handle missing observations under the missing-at-random assumption without requiring complete cases or sphericity.

Exploratory multivariable analyses will be performed to investigate associations between clinical outcomes and sociodemographic and surgical-related variables, focusing on relationships with surgical procedures. Potential confounding effects of graft type and concomitant procedures on early quadriceps outcomes will not be formally tested, and any subgroup analyses will be limited to descriptive reporting.

A two-sided significance level of α = 0.05 will be adopted, and results will be reported with 95% confidence intervals.

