Third, this study focuses on short-term outcomes assessed up to seven days post-intervention, which aligns with typical follow-up durations reported in the literature for PENS interventions [34,35,40]. While this design is suitable for evaluating early neuromuscular effects in the postoperative phase, it does not allow conclusions regarding the persistence of these effects or their influence on longer-term functional recovery following ACLR.

Finally, variability in individual response to neuromodulatory interventions, as well as potential heterogeneity in graft type and associated surgical procedures (meniscal procedures or lateral extra-articular reinforcement), may influence short-term outcomes. These factors should be considered when interpreting the findings and planning future studies.

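### Graft type is neither a stratum nor a term in the stated mixed model, so between-arm comparisons of QMVIC level with 18 per arm are open to chance imbalance that one prespecified covariate would handle (minor)

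*Protocol article*

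**What the plan says.** - **Eligibility (section 2.4).** Patients qualify after reconstruction "using hamstring tendon (HT), patellar tendon (BPTB), quadriceps tendon autografts, or allografts". Meniscal procedures and a lateral tenodesis are also allowed.
- **Randomisation (section 2.5).** "Block randomization with a block size of three will ensure an equal number of participants across the three study groups". On strata: "Stratified randomization by graft type or concomitant procedures was not implemented; participants were randomized without stratification to maintain study feasibility and integrity". Section 2.3 gives 18 per group.
- **Endpoint (section 2.8.1).** Highest quadriceps force of the operated limb in newtons, not normalised to body mass or lever arm.
- **Baseline data (section 2.8).** Graft type is already recorded.
- **Analysis (section 2.9).** "These models will include the fixed effects of group, time, and the group × time interaction". The pre-treatment visit A1 is one of the four levels of time. The section adds that confounding by graft and concomitant procedures will not be formally tested. Surgical variables enter only exploratory multivariable analyses, and subgroup results are descriptive.
- **Limitations (section 3.2).** The protocol accepts that "potential heterogeneity in graft type and associated surgical procedures (meniscal procedures or lateral extra-articular reinforcement), may influence short-term outcomes".

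**The concern.** The eligibility rule mixes patients whose graft came from the muscle-tendon unit being tested with patients whose graft did not, and the endpoint is the absolute force of that unit. The protocol itself allows that graft may influence short-term outcomes. Graft could be accounted for by stratification or by a model term, and the plan uses neither.

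With 18 per arm the mix can differ noticeably between an active arm and control. If it does, a reader may attribute a difference in quadriceps force, or its absence, to graft. An adjustment added after the imbalance has been seen would be post hoc; one named now would not.

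**Working it through.** **Inputs from the protocol.** 18 per arm (section 2.3); blocks of three without strata (2.5); four visits with A1 as a level of time, and a model of group, time and group × time (2.9). The protocol gives no graft share and no graft effect, so there is no figure of its own to reproduce here.

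**Assumptions.** Share of extensor-mechanism grafts p = 0.3 to 0.5. Stable effect of such a graft on force d = 0.5 to 1.0 within-graft SD.

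**1. Chance imbalance.** The number of extensor-mechanism grafts in each arm was drawn as Binomial(18, p), with 400,000 draws per value of p.

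| p | A given active arm differs from control by ≥4 | At least one active arm does |
|---|---|---|
| 0.3 | 0.202 | 0.335 |
| 0.4 | 0.233 | 0.383 |
| 0.5 | 0.244 | 0.399 |

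At p = 0.2 the last column falls to 0.242.

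**2. Comparison of QMVIC levels at one visit.** Shift from a 4-of-18 imbalance = (4/18) × d:
- d = 0.5: 0.222 × 0.5 = 0.11 SD
- d = 1.0: 0.222 × 1.0 = 0.22 SD

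Graft adds v = p(1−p)d² to the between-patient variance, so leaving it out inflates the standard error by √(1 + v):
- p = 0.3, d = 0.5: v = 0.21 × 0.25 = 0.0525; √1.0525 = 1.026, or about 3%
- p = 0.5, d = 1.0: v = 0.25 × 1 = 0.25; √1.25 = 1.118, or about 12%

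**3. Change from A1 (group × time).** A stable graft effect is present at A1 and at each later visit, so it subtracts out. One trial of 54 patients was simulated (p = 0.4, graft effect −0.8, random intercept) and fitted three ways:

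| Model | Group × time, estimate (SE) | Between-arm level term, SE |
|---|---|---|
| As in section 2.9 | −0.353 (0.311) | 0.371 |
| Plus graft | −0.353 (0.311) | 0.335 |
| Plus graft and graft × time | −0.347 (0.314) | 0.336 |

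The graft main effect leaves the change contrast untouched and cuts the SE of the level contrast by about 10% (0.335/0.371 = 0.90). Adding graft × time costs the change contrast about 1% in SE (0.314/0.311 = 1.01). With ANCOVA on A1, adding graft gains at most about 2%.

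**4. Grafts that change differently over seven days.** If the difference in change is 0.2 to 0.4 SD (an assumption), a 4-of-18 imbalance shifts the change contrast by 0.222 × 0.2 = 0.04 to 0.222 × 0.4 = 0.09 SD. A 5-of-18 imbalance gives 0.06 to 0.11 SD. Only graft × time or stratification addresses this; a graft main effect does not.

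**The case against.** The strongest reply is that the repeated-measures structure already does the work. Each participant is their own control, so a stable strength deficit from the graft is in A1 and drops out of group × time. This stands: for that contrast a graft main effect gains nothing. A reader might take the 0.11-0.22 SD as the error in the treatment effect generally, and the model in section 2.9 does not support that. What remains is that section 2.9 names neither a primary contrast nor a primary visit and plans Bonferroni post hoc comparisons, so comparisons of levels at A2-A4 and the group main effect stay open.

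It can also be said that the choice is deliberate and disclosed, and that stratifying 54 patients on four grafts plus tenodesis and meniscal procedures is impractical. Both points are fair. They excuse the absence of full stratification, but not of a two-level covariate already collected.

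Further, the documents call graft only a possible influence, name other procedures beside it, and nowhere say that extensor-mechanism grafts lower QMVIC. A reader might infer a known predictor of the outcome; that goes beyond the text. The case for graft over the other recorded factors rests on anatomy and on its low cost.

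Finally, covariates are often left to an analysis plan that is not shown. But section 2.9 lists the model terms and says that graft confounding will not be formally tested, so this is a stated position and not silence.

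**Conclusion.** The point holds as a minor one. The plan leaves a recorded baseline factor, which it considers possibly influential, out of both the randomisation and the stated model.

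A reader might infer that the missing strata bias the trial. They do not: randomisation is valid without them, and the confidence interval already allows for chance imbalance. Nor is a marked imbalance likely in the sense of better than even odds; a 4-of-18 difference in at least one control comparison has roughly a one-in-three chance (34-40%) under the assumed shares.

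The size depends on the contrast. For QMVIC levels, such an imbalance shifts the comparison by 0.11-0.22 SD, and omitting graft inflates the standard error by about 3-12%. For change from A1, the cost is nil if the graft effect is stable and small if grafts differ in seven-day change. All of these figures rest on assumed graft shares and effects, since the protocol gives neither.

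**What to change.** In section 2.9, add to the primary mixed model one prespecified binary baseline covariate, extensor-mechanism autograft (patellar or quadriceps tendon) versus hamstring autograft or allograft, together with its interaction with time. Amend the sentence on not formally testing graft so that it agrees. Exploratory questions about whether the treatment effect differs by graft can stay exploratory.

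Randomisation need not change and no new data are needed. The cost is a few degrees of freedom and about 1-2% in standard error if graft is not prognostic. If the sponsor names change from A1 as the primary contrast, the gain is small: mainly cover against grafts that change differently over the week.

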### 2.6. Blinding

Due to the study design, the treating clinician cannot be blinded to group allocation. However, the outcome assessor will remain blinded to group allocation throughout the study period to maintain objectivity in data collection and analysis.

To minimize the risk of assessor unblinding, the assessor will not be present in the clinical setting during intervention delivery, and the clinician will remind participants not to disclose their assigned intervention during outcome assessments. Although the invasive nature of PENS may pose a theoretical risk, these procedures are expected to maintain assessor blinding throughout data collection.

To formally evaluate blinding integrity, the assessor will be asked at each outcome assessment (A2: immediately post-intervention; A3: 24 h post-intervention; and A4: 7 days post-intervention) to guess each participant’s group allocation and provide a confidence in this judgment. This procedure will allow monitoring of blinding effectiveness, particularly given that participant and treating clinician blinding is not feasible.

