All interventions will be delivered by the same experienced clinician specialized in invasive physiotherapy techniques. The Duo Tens Globus^®^ electrostimulator (Fisiomundo Tecnología Médica y Rehabilitación SL, Alicante, Spain) will be used to deliver a biphasic, symmetrical, square waveform current to the targeted motor points [45,60].

Once participants provide written informed consent, the blinded assessor will perform the baseline assessment (A1). Immediately afterward, the assessor will leave the clinical setting, and the clinician, if applicable, will administer a single 30 min TENS session or a single 5 min LTP PENS session. The clinician will also instruct all participants on the guidelines for performing the CRP over the following 7 days, which will constitute the total duration of the program. Table 1 summarizes the key characteristics of the interventions applied in each study group, highlighting the differences between the control group, the TENS group, and the PENS group.

Control Group: Participants will perform CRP only.

TENS Group: During the sixth postoperative week, participants will perform CRP and receive a single high-frequency TENS session. Two surface electrodes (5 × 5 cm) will be placed over the distal zone of the middle third of the vastus medialis and distal zone of the proximal third of the vastus lateralis [61,62]. Stimulation parameters will be 100 Hz frequency, 200 μs pulse width, intensity adjusted to each participants’ pain threshold, and duration 30 min. Participants will be allowed to adjust intensity during the session.

The TENS protocol specifies a reproducible criterion for adjusting intensity by increasing pulse amplitude to achieve a strong but comfortable sensation [60], tailored to each participant’s tolerance threshold and consistent with the scientific literature [30,32,63,64]. Moreover, evidence suggests that higher intensities produce greater effects and may prevent analgesic tolerance [30,32,63,65].

No predefined intensity algorithm will be used; however, the clinician provides consistent instructions for all participants in the TENS group to adjust stimulation according to their individual pain threshold during administration, ensuring standardized delivery.

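### Sealed envelopes do not ensure that allocations in fixed, published blocks of three are unpredictable, because the protocol does not keep knowledge of past assignments away from enrollment

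*Protocol article*

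**What the plan says.** Section 2.5 (Allocation and Randomization) fixes the block size and composition: "A total of 54 participants will be allocated in 18 blocks of three, with each block containing one assignment to each group". There is a single list for the whole trial, since "participants were randomized without stratification to maintain study feasibility and integrity". Concealment rests on sequentially numbered cards: "The cards will be placed in sealed opaque envelopes, which will be opened only after baseline assessments are completed by an independent assessor". The section then draws the conclusion at issue: "This approach prevents recruitment and enrollment personnel from predicting future allocations, even with block randomization of size three".

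Three other places bear on who knows what:

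- Section 2.6 (Blinding) says that "the treating clinician cannot be blinded to group allocation". It keeps the assessor away while treatment is given, has participants reminded not to reveal their arm, and records the assessor's guess of the arm, with confidence, at A2, A3 and A4.
- Section 2.7 (Interventions) says "All interventions will be delivered by the same experienced clinician". The same clinician gives all participants, controls included, their instructions for the rehabilitation program.
- Section 2.2 has the principal investigator reading records and contacting patients. It does not say whether this is the treating clinician or someone else.

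The only role that section 2.5 separates from recruitment is that of the statistician who generates the list.

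**The concern.** A sealed envelope hides the next card. It does not hide what follows from cards already opened. When every block holds exactly one of each arm and the block size is published, two known assignments fix the third and one known assignment excludes an arm for the second. The assurance in section 2.5 is about prediction, and sealing the envelopes does not remove this route to it.

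The decision to enroll is what is at stake. Someone who knows that the next patient will go to a given arm could, knowingly or not, affect whether or when a borderline patient enters. Section 2.4 leaves some room for judgement, for example on contraindications and on the ability to complete questionnaires reliably. With 18 patients per arm and an effort-dependent primary outcome (hand-held dynamometry with verbal encouragement, no sham), a few selectively entered patients could matter.

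**Working it through.** **Inputs, all from the protocol article.** Block size 3 with one of each arm, 18 blocks, 54 participants, no stratification (section 2.5); one centre (section 2.1); one unblinded clinician who meets all participants (sections 2.6 and 2.7).

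**The plan's own figure.** 18 × 3 = 54, so 18 per arm. This reproduces.

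**Predictability with fixed blocks of three.** Take an observer who knows the block size and all earlier assignments, and who always guesses the arm with most places left in the block.

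- First in block: three arms possible, probability of a correct guess 1/3.
- Second in block: two arms possible, probability 1/2.
- Third in block: one arm possible, probability 1.

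Certain allocations: 18 blocks × 1 = 18 of 54 = 33.3%.

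Expected correct guesses: 18 × (1/3 + 1/2 + 1) = 18 × 11/6 = 33 of 54 = 61.1%.

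Under unrestricted 1:1:1 randomization: 54 × 1/3 = 18 of 54 = 33.3% correct, none certain.

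**Alternatives.** The same observer was applied to other schemes. Fixed sizes were enumerated exactly. Mixed sizes were simulated (4,000 runs, sizes drawn with equal probability, and an observer who knows the set of sizes but not their order and updates by Bayes' rule).

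| Scheme | Certain, of 54 | Correct guesses, of 54 |
|---|---|---|
| Fixed 3 (the plan) | 18.0 (33%) | 33.0 (61%) |
| Fixed 6 | 10.8 (20%) | 30.3 (56%) |
| Fixed 9 | 7.7 (14%) | 28.7 (53%) |
| Random 3/6/9 | about 1.9 (4%) | about 29.7 (55%) |
| Random 6/9 | about 2.7 (5%) | about 29.1 (54%) |
| Unrestricted | 0 | 18.0 (33%) |

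Varying the block size removes nearly all certain allocations. It lowers average guess accuracy only modestly, because any blocking leaves some information in the running counts.

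**Who could make the deduction.** The treating clinician has the complete history from sections 2.6 and 2.7. Recruiters have it only if they are that clinician or are told. The text neither states nor excludes this.

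**The case against.** The sentence in section 2.5 is about recruitment and enrollment staff, whereas the person shown to know every assignment is the treating clinician. No section says that this clinician recruits, screens or obtains consent. If recruiters are different people who never learn past assignments, they cannot deduce the third card, and the sentence would be true of them. This stands. A reader might infer that the assurance is simply false, or that a third of the allocations will be biased, and the documents support neither.

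Other limits also stand:

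- Certainty requires that both earlier envelopes of a block were opened before the third patient is enrolled.
- Room to reorder patients is small. The intervention falls in the sixth postoperative week, which the date of surgery largely determines. Discretion over whether to enroll remains.
- A reader might suppose that baseline effort could be steered. Baseline is measured by a blinded assessor before the envelope is opened, and the clinician is not described as taking part, so the text gives no direct route.
- A reader might conclude that assessor blinding fails. An assessor who inferred two arms of a block could infer the third, but section 2.6 both limits this and monitors it through the recorded guesses.
- It would be too strong to call any resulting bias undetectable. Baseline strength and the surgical and demographic variables are collected, so gross selection on these could be seen and partly absorbed in the analysis. Selection on unmeasured factors could not.

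What the objection does not supply is a safeguard that supports the categorical sentence. Opening envelopes after baseline protects the baseline measurement, but the decision to enroll has been taken by then.

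**Conclusion.** The point holds in conditional form. The unpredictability asserted in section 2.5 is not ensured by the method described. With the block size and composition published, 18 of 54 allocations (33%) are certain, and 61% can be guessed correctly on average, for anyone who knows the earlier assignments in the block. At least one person at the site does, and the protocol does not keep that person, or that knowledge, out of enrollment.

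Whether selection bias results depends on an assumption that the documents leave open: that the clinician recruits, influences whether or when a patient enters, or shares past assignments with those who do. The figures 33% and 61% measure predictability. They are not estimates of bias in the treatment effect.

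**What to change.** 1. Have the independent statistician generate the list, or its unopened remainder if recruitment has begun, with randomly varying block sizes, for example 3, 6 and 9. Neither the sizes nor their order should be disclosed to site staff. Certain allocations fall from 33% to about 4%. Average guess accuracy falls only from 61% to about 55%, so this should not be presented as a complete cure.
2. State in section 2.5 or 2.6 that the treating clinician takes no part in recruitment or eligibility decisions, and that those who recruit are not told past assignments. This costs little and addresses the mechanism directly.
3. Delete the sentence on unpredictability, or qualify it to say what sealing the envelopes does protect.

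The cost is a new list and a new set of envelopes. Arm sizes may differ slightly if recruitment stops within a block.
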